## Abstract

**Background:**

Adverse childhood experiences (ACE) are linked to an increased risk of psychological disorders and lower psychosocial functioning throughout life. This study aims to evaluate the FACE self-help app, designed to promote resilience and well-being in emerging adults with a history of ACE. The app is based on cognitive-behavioural principles and consists of two thematic components: (1) self- and emotion regulation (SER) and (2) social skills and biases in social information processing (SSIP).

**Methods:**

The efficacy of the app will be tested through a single-centre, two-arm randomized controlled trial, comparing an active intervention group against a waiting list control group. The active group is divided into two subgroups, in which the two components are delivered in a different order to investigate differential effects in a crossover design. Up to 250 emerging adults aged 18 to 25 years with a history of ACE from a general population cohort study will be recruited. The primary objective is to test the efficacy of the app in improving resilience (primary outcome) and well-being (co-primary outcome) compared to a waiting list control group and to examine the stability of these effects. The secondary objectives include testing the efficacy of the app in improving the secondary outcomes, i.e., self-efficacy in managing emotions, problem solving, fear of evaluation, social avoidance, and self-esteem; examining the differential effects of the two components; and assessing the effect of the app on real-life data on resilience, affective states, distress in social interactions and coping strategies. Furthermore, the study will investigate potential moderators (e.g. ACE severity) and mediators of intervention outcomes (e.g. self-efficacy in managing emotions).

**Discussion:**

The results will provide insights into the efficacy of the self-help intervention as well as mediators and moderators of outcomes. Furthermore, results will extend the existing knowledge by testing the differential effects of the SER and SSIP component on the outcomes. Findings can inform improvements to the FACE app and the development of other interventions for this target group and assess its potential as a scalable, low-threshold intervention to support emerging adults with a history of ACE in their transition to adulthood. Trial registration number: NCT05824182.

## Background

One out of three children worldwide experiences adverse childhood experiences (ACE) such as emotional, physical or sexual abuse, emotional or physical neglect or exposure to intimate partner violence [1]. It is well established that ACE have detrimental effects on mental and physical health throughout the lifespan. Therefore, primary prevention of the occurrence of ACE and early interventions in childhood are paramount. However, there are limitations to these approaches. Preventive interventions generally require the collaboration of parents or legal guardians, which cannot always be expected. Furthermore, meta-analyses have yielded conflicting results regarding the efficacy of prevention targeted at parents [2, 3].

Later in life, the transition from adolescence to young adulthood offers a window of opportunity for selective prevention directly targeting individuals affected by ACE. Emerging adults are better able to distance themselves from an adverse family environment and have more control of their own lives [4]. Multiple transitions, such as entering new stages of professional or educational life, moving away from one’s parents and shifting from economic dependence to independence, offer turning points and opportunities for redirecting maladaptive trajectories into healthier paths [5]. At the same time, this stage in life also holds a risk of the consolidation of problems, deterioration of trajectories or the onset of destructive outcomes, such as substance use, sexual risk behaviour, unemployment, deliberate self-harm and suicide [6–8]. Interventions at this stage in life are thus likely to have a large impact and offer high potential for preventing the need for more intensive psychotherapy for later chronic dysfunctions. Still, this critical phase is often accompanied by a gap in health and social service delivery for emerging adults: as they are no longer supposed to use services for children and adolescents, a change to the adult health service system might not appropriately address the needs of vulnerable emerging adults [9]. Additionally, the gap between the need for and the provision of care is assumed to be especially large for children, families and adults with dysfunctions associated with traumatic experiences and ACE [10, 11].

Digital self-help interventions (e-health) or interventions delivered on smartphones (mobile- or m-health) may bridge the resulting gap, as they are scalable, affordable and a convenient, user-friendly, low-threshold, anonymous and immediate way of delivering interventions in daily life [12]. Digital self-help and m-health interventions have been shown to improve resilience, well-being and emotion regulation and decrease symptoms of distress, depression, and anxiety [13–17]. Nevertheless, the effects were often only small to moderate; many m-health interventions lack a theoretical basis and additional studies with general population samples are needed [13, 16]. Moreover, digital interventions often result in low engagement, high attrition, and substantial dropout [18, 19]. Thus, improving users’ acceptance of the digital intervention is highly relevant for ensuring long-term usage. Nevertheless, a study suggested that more than 70% of adolescents would use an e-health intervention and that 32% would prefer an e-health intervention over traditional face-to-face support [20].

Fostering resilience, self- and emotion regulation as well as social information processing can present meaningful transdiagnostic targets for e- or m-health interventions. Resilience, defined as the ability of a person to function successfully despite aversive experiences and to adapt to a difficult situation, is a key protective factor against the negative health consequences of ACE [21, 22] and may thwart the development of mental health problems [23]. Pronounced resilience protects against negative consequences, while the experience of ACE is generally associated with lower resilience [23, 24]. Thus, to minimize negative effects on health, it is essential to promote the resilience of people affected by ACE through appropriate interventions [24].

Furthermore, self- and emotion regulation are crucial targets for interventions for emerging adults with a history of ACE. Emotion regulation has been conceptualized as part of the broader concept of self-regulation. The self-regulation promotion model identifies behavioural skills (e.g. stress management, impulse control, or goal setting and planning), cognitive skills (e.g. problem-solving, self-reflection, appraisal/reappraisal) and emotional skills (e.g. recognizing cues for distress, self-calming strategies, or acceptance of emotions) as targets for promoting self-regulation [25]. For the developmental stage of emerging adulthood in general, Murray and colleagues suggested providing guidance for complex problem solving and support for coping with significant stressors [25]. Emerging adults with a history of ACE may benefit especially from such interventions: ACE were associated with less adaptive emotion regulation [26, 27] and dysfunctional emotion regulation was found to mediate the association between ACE and mental and physical health problems [28–30]. Moreover, emotion regulation skills also affect the resilience of a person [31–33]. ACE were also associated with decreased problem-solving and coping skills [27]. Thus, improving self- and emotion regulation strategies seems to be a promising strategy for mitigating the negative consequences of ACE [28].

Related to self- and emotion regulation, self-esteem was found to be a mediator of the association between emotion regulation strategies and resilience among emerging adults [34]. ACE correlated negatively with self-esteem [35]. Low self-esteem, in turn, has a negative impact on mental health [36] and there is a consistent link between self-esteem and psychopathology [37]. Self-esteem has been shown to be a mediator between ACE and depression, loneliness, perceived stress and life stress [38], between child maltreatment and depressive symptoms [39] and between child maltreatment and well-being [40].

In addition to self- and emotion regulation, social skills and social information processing are important factors for fostering resilience and coping with ACE. ACE were associated with less adaptive social cognition and biased social information processing [41, 42]. Moreover, lower social support and loneliness have been established as a mechanisms linking ACE to adolescent or adult well-being and psychopathology [43–48].

### The present study

The FACE study focuses on self- and emotion regulation and social information processing as links between ACE and psychosocial functioning and as key components for fostering resilience. These components are in line with the transdiagnostic model of mechanisms linking childhood trauma to psychopathology that describes social information processing (enhanced threat detection and hostile attribution bias) and emotion processing (heightened emotion reactivity and poor emotion regulation) as malleable mechanisms linking childhood trauma to internalising and externalising psychopathology and that social support can act as a protective factor [49]. While there are many other factors that can influence the consequences of ACE such as biological, cognitive, or environmental factors, self- and emotion regulation and social information processing have consistently been associated with poorer mental health and there are several evidence-based interventions that target these factors.

The FACE study consists of two interlinked subprojects: (1) a three-wave epidemiological study to investigate emotion regulation and social information processing as mechanisms that link ACE with psychosocial functioning in emerging adulthood [50] and (2) the FACE intervention study, which is presented in this study protocol. The development of a specific transdiagnostic intervention for emerging adults with a history of ACE is important for several reasons: Participants may benefit from specific information about ACE and ACE-related content to develop a better understanding of their experiences. We also expect that a specific intervention addressing frequent questions, problems and needs of emerging adults with a history of ACE leads to higher enrolment, adherence, and efficacy of the intervention. Moreover, emerging adults with a history of ACE present a wide range of clinical and subthreshold symptoms including depressive, anxious and Posttraumatic Stress Disorder symptoms which suggests a transdiagnostic approach for interventions. Traditional e-health interventions are often designed for specific disorders and require the presence of this clinical diagnosis as inclusion criteria. The FACE intervention study is the first clinical trial of a specific m-health intervention targeted at emerging adults with a history of ACE and explores moderators and mediators of the intervention outcome. It not only uses retrospective self-report questionnaires to evaluate the intervention, but also ecological momentary assessments (EMA) to collect repeated real-time data of affective states and social interactions in a natural environment. Thus, the FACE study extends the existing knowledge on self- and emotion regulation and social information processing as mechanisms for fostering resilience in emerging adulthood.

## Methods

### Objectives

The primary objective is to test the efficacy of the FACE self-help app in improving resilience (primary outcome) and well-being (co-primary outcome) in emerging adults with a history of ACE compared to a waiting list control group (see Fig. 1). Then we aim to test the stability of the effects across three months in the intervention group. We hypothesize that the intervention group will significantly improve in all outcomes compared to the waiting list control group and that these outcomes will be stable.

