### Measures

#### Primary and secondary outcomes

All primary and secondary outcomes will be measured via online self-report questionnaires. Participants will be asked to complete them before the intervention (t0), 5 weeks after starting the intervention (t1, intermediate measurement), which will correspond to the time needed to complete the first component, and 11 weeks after starting the intervention (t2). By this time, participants will have completed both components of the intervention, which corresponds to the post-measurement. Furthermore, participants will be asked to complete the questionnaire again 11 weeks after finishing the FACE self-help app, which serves as a follow-up (t4). An exception is the adapted Patient Satisfaction Questionnaire, which will be assessed only after the finishing first component (t1), and after finishing the second component of the self-help app (t2). Reminders to fill out the questionnaire will be sent after 2 and 4 weeks.

***Resilience*** will be assessed with the 10-item German version [51] of the Connor-Davidson Resilience Scale (CD-RISC) [21], which has been shown to be a valid and reliable measurement [51, 52]. The CD-RISC is widely used and has been shown to be sensitive to change following interventions [21, 53]. The items are rated on a 5-point scale ranging from 0– Not true at all to 4– True nearly all the time.

***Well-being*** will be assessed with the Warwick-Edinburgh Mental Well-being Scale (WEMWBS) [54]. The German version of the scale shows good reliability and validity [55]. The scale contains 14 items that are rated on a 5-point scale ranging from 1– never to 4– always.

***Self-efficacy for managing emotions*** will be assessed with the PROMIS Short Form v1.0 - Self-Efficacy for Managing Emotions [56]. PROMIS items were developed for use in the general population for different aspects of mental health. Method and assessment timepoint: The scale contains 7 items that are rated on a 5-point scale ranging from 1– never to 4– always.

***Fear of negative evaluation*** will be assessed with the German short version of the Fear of Negative Evaluation Scale (SANB-5) [57]. The scale contains 5 items that are rated on a 4-point Likert scale from 1 - almost never true to 4- almost always true.

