### Study intervention

The FACE app is based on a transdiagnostic model of mechanisms linking childhood trauma to psychopathology and addresses the thematic components Self- and Emotion Regulation (SER) and Social Skills and Social Information Processing (SSIP) for the promotion of resilience and well-being. It was developed based on well-established cognitive-behavioural principles that have been used in other web-based self-help apps [13] and offers psychoeducative materials and exercises in various formats (text, audio, video).

In addition to two components SER and SSIP (see Fig. 1), there are two additional parts intended to frame the user’s experience: an introduction and a conclusion/farewell. First, the general introduction, available to everyone from the start, explains the app interface, presents general information on ACE (psychoeducation about prevalence, types, and consequences), and encourages reflection on one’s personal status and resources plus the formulation of personal goals for the app. Towards the end of the intervention, the conclusion/farewell encourages the revisiting of the goals and ideas of the start and the reflection on what was most helpful while using the app. In addition, a collection of short activities and exercises relevant to everyday life and promoting physical and mental well-being is accessible as a toolbox at all times, but also referred to at relevant moments throughout the rest of the content.

Within each of the two thematic components SER and SSIP, four different modules include informational reading on ACE and ACE-related topics, as well as prompts for participants to actively reflect on what was learned in the readings and exercises to apply their knowledge and practice skills (see Table 1). The first module includes information about ACE in relationship with SER or SSIP respectively. Modules 2 and 3 contain information about the theoretical background of SER or SSIP respectively as well as information, writing tasks and exercises on the modification of possible cognitive biases. In module 4, the focus is on learning new skills and their implementation/transfer in daily life. Participants are encouraged to work through one module per week and to complete the exercises, which adds up to approximately one hour of engagement with the app per week.

**Table 1 Tab1:** Outline of the components of the FACE self-help app

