#### Participants’ support and guidance

During the 10 weeks of the use of the FACE self-help programme, participants will receive weekly written feedback and support via an integrated messenger function - either from a psychologist or social worker of the School of Social Work at the University of Applied Sciences and Arts Northwestern Switzerland or from trained and supervised master students in Clinical Psychology of the University of Bern. This weekly support, which was short but individualised in terms of progress and focus, acknowledges and motivates participants in their engagement with the app, keeping emphasis on positive reassurance. It aims to improve adherence, provides a weekly structure, support for technical problems and the possibility to ask further questions. If needed, stabilising interventions via phone calls are offered by a psychologist within the FACE team who can also, if needed, provide support with seeking more comprehensive treatment through counselling services, psychotherapists or psychiatrists close to where the participants live. Reports of adverse events and negative effects will be collected.

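### The stability aim is set at three months, but the scheduled follow-up comes only about 11 weeks (possibly 10) after the post-measurement

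*Protocol article*

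**What the plan says.** The Objectives section of the protocol article follows the primary efficacy comparison with an aim to "test the stability of the effects across three months in the intervention group", and adds the hypothesis that the outcomes will be stable.

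The section on primary and secondary outcomes sets the schedule in weeks:

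- The post-measurement falls at "and 11 weeks after starting the intervention (t2"), and the text adds: "By this time, participants will have completed both components of the intervention, which corresponds to the post-measurement".
- For the follow-up, participants are to "complete the questionnaire again 11 weeks after finishing the FACE self-help app, which serves as a follow-up (t4").

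The section on participants' support and guidance gives a length for the programme: "During the 10 weeks of the use of the FACE self-help programme".

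The section on missing data and dropout says that everyone who has not actively withdrawn will be invited to the post- and follow-up questionnaires.

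**The concern.** The objective and the schedule give different lengths for the same period. Stability is judged by comparing t4 with t2, so the claim can reach no further than the time between those two assessments. If that time is 10 or 11 weeks, a report that effects held for three months would name a period the data do not cover. The aim sits in the primary-objective paragraph and carries a hypothesis, so the figure is likely to reach the conclusions.

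The wording of the two time points adds a smaller problem. One is counted from starting the intervention and the other from finishing the app. The article does not say outright that finishing means a scheduled date, and it gives both a 10-week period of use and a post-measurement at week 11. The t4 date is therefore not fixed to the week.

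**Working it through.** **Inputs**

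- Stated stability period: three months (Objectives).
- t2: week 11 after start (Primary and secondary outcomes).
- t4: 11 weeks after finishing the app (same section).
- End of app use: by week 11, since both components are complete by t2 (same section), or week 10 if the programme length in the support section marks the end.

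**Step 1: the stated figure in weeks.** 3 × 365.25 / 12 / 7 = 13.04 weeks, about 91 days.

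**Step 2: the interval that the schedule gives.** Let F be the week in which the app ends.

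t4 = F + 11, so t4 − t2 = (F + 11) − 11 = F.

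| App ends (F) | t4 | t2–t4 interval | In months | Short of 13.04 weeks by |
|---|---|---|---|---|
| Week 11 | week 22 | 11 weeks (77 days) | 2.53 | 2.04 weeks, 15.7% |
| Week 10 | week 21 | 10 weeks (70 days) | 2.30 | 3.04 weeks, 23.3% |

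With three months taken as a round 91 days, the shortfalls are 1 − 77/91 = 15.4% and 1 − 70/91 = 23.1%.

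**Step 3: can any reading reproduce three months?** Because the interval equals F, 13 weeks would need the app to end at about week 13. That is two weeks after t2 and contradicts the statement that both components are complete by then. Counting from the end of the app instead of from t2 gives 11 weeks by definition. The stated figure is not reproduced on any on-schedule reading.

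**Step 4: one calendar anchor.** If t4 is set 11 weeks after the t2 due date, t4 = 11 + 11 = week 22 and the nominal interval is 11 weeks for everyone, whatever their own pace. A true three-month interval from t2 would put t4 at 11 + 13 = week 24.

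**The case against.** The best reply is that three months is loose rounding of 11 weeks, and that a paper reporting t4 as the outcomes section defines it would not mislead anyone. Nothing in the sample size rests on the interval, the stability test is confined to the intervention group, and the abstract gives the stability aim no duration. Fig. 1, which is not shown, may also set out the schedule. Most of this stands, and it keeps the point small. It does not remove it: the article otherwise states its timings in weeks, and two sections of the current text still disagree.

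A reader might go further and infer that the follow-up interval depends on adherence and so flatters stability. The argument would run as follows:

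- Someone working at one module per week ("Participants are encouraged to work through one module per week and to complete the exercises") could end the eight thematic modules at week 8, leaving 8 weeks to t4.
- Someone answering t2 only at the four-week reminder ("Reminders to fill out the questionnaire will be sent after 2 and 4 weeks") would leave 21 − 15 = 6 or 22 − 15 = 7 weeks.
- Someone who never finishes would have no t4 date at all.

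The document does not support that reading:

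- It uses completion wording as a label for fixed calendar points. The satisfaction questionnaire, for instance, is placed after finishing the second component and labelled t2. Finishing the app is most naturally the scheduled end, not each person's own date.
- Follow-up invitations go to all who have not withdrawn, so they do not hang on finishing.
- The reminder sentence is not limited to t2. A person four weeks late at both time points has 26 − 15 = 11 weeks, unchanged, and lateness at t4 alone lengthens the interval.
- Even on the individual reading, slow finishers would have a longer interval, so no net direction of bias is shown.

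**Conclusion.** The mismatch holds. The objective states three months, while the schedule gives a t2–t4 interval of 11 weeks, or 10 if the app ends at week 10. The shortfall is 2 to 3 weeks, roughly 15% to 23%.

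This rests on assessments taken on their due dates and on three months meaning about 13 weeks. If three months is assumed to mean 12 weeks, the shortfall is 1 to 2 weeks (1/12 = 8% to 2/12 = 17%), smaller but still present.

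The different reference points in the wording call for clarification; they are not evidence of bias. Adherence-dependent intervals, intervals of 6 to 8 weeks and an undefined follow-up for non-finishers all rest on assumptions that the text does not make, and are not part of this conclusion. The matter deserves correction because it fixes the period the trial can claim, but it does not threaten the efficacy comparison.

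**What to change.** - Define t4 as 11 weeks after the t2 due date, week 22 after start, for everyone randomised to the app, finishers or not. This agrees with the rule that all who have not withdrawn are invited.
- Restate the objective, and any later durability conclusion, as covering 11 weeks.
- Reconcile the 10-week period of use with the week-11 post-measurement, so that the scheduled end of the app is unambiguous.
- Report the distribution of actual days between t2 and t4.

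The cost is a few words in the protocol, a fixed invitation date and one descriptive line in the report. If the team wants to keep the three-month claim, it can instead move t4 to week 24, which lengthens follow-up by about 2 to 3 weeks per participant. That is optional, since restating the period already resolves what is shown here.
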